### Randomization

To randomize participants to the two intervention arms, a randomization sheet generated by a random digit generator is used (http://www.randomizer.org). Throughout the recruitment process, the list of randomized numbers will be assigned to participants by the research coordinator in sequential order from 1 to 154 in the order in which participants completes the baseline CHIP appointment. Once a participant is assigned a condition, the research coordinator enters the date and the participant’s initials next to the condition on the randomization sheet. This information together makes up the participant’s anonymous intervention code. Participants are told that the study evaluates two different approaches to lifestyle changes to see if one is superior to the other. Throughout the recruitment process, groups of approximately 6 to 10 people will be created according to their language (i.e., French or English), location, and time of day preferences. It was inherently not possible to blind the interventionist to interventions. However, the staff assessing the outcome variables (e.g. weight, EST) is blind to which intervention the participants were assigned.

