### Participant recruitment

Participants are recruited through: (1) flyers and information pamphlets that will be distributed at various clinics, hospitals, and pharmacies; (2) personal communications with the research team, including the nurses and physicians who refer patients to the CHIP and additional local physicians who are in contact with potential eligible participants; (3) emails to 700 individuals who previously were enrolled in one of CHIP’s programs; (4) emails to the members of the YW-YMHA in which the CHIP is located; (5) electronic newsletters of various universities and institutions around Montreal; and (6) advertisement through social media. Interested individuals will contact the research coordinator through email or the phone number published in the information materials.

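### The allocation procedure as described has no concealment step: the coordinator who receives volunteers also assigns them in sequence from a sheet that carries the conditions

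*Protocol article*

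**What the plan says.** The protocol article describes the procedure in three places.

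- **Participant recruitment:** "Interested individuals will contact the research coordinator through email or the phone number published in the information materials".
- **Determining eligibility:** the third step is one appointment with a medical exam and an exercise stress test. Baseline measurements and random assignment take place at that same appointment.
- **Randomization:** "a randomization sheet generated by a random digit generator is used". Then "the list of randomized numbers will be assigned to participants by the research coordinator in sequential order from 1 to 154". Rows are taken up as people finish their baseline visit. After each assignment, "the research coordinator enters the date and the participant’s initials next to the condition on the randomization sheet". On the participant code: "This information together makes up the participant’s anonymous intervention code". On outcome assessment: "the staff assessing the outcome variables (e.g. weight, EST) is blind to which intervention the participants were assigned".

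Trial status adds that recruitment was still open in May 2014.

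**The concern.** A random sequence protects the comparison only if those who enrol participants cannot see what comes next. Here one role has contact with volunteers and also works down the list. Someone who knows the next arm can, without intending to, encourage one volunteer more than another, read a borderline exclusion differently, or let an appointment fall earlier or later. The arms would then differ in prognosis at baseline. The primary comparison of percent weight loss would carry that difference. Adjustment for measured baseline factors could reduce it but would not reach unmeasured ones; motivation, an obvious candidate, is not among the measures in Table 1.

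The code raises a second, smaller question. If it contains the condition, any record that carries it reveals the arm to whoever handles the record.

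**Working it through.** The point is procedural, so the check is a reading of the passages against each other.

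**1. Can the next arm be known?** The sequence exists in advance on a sheet. The coordinator writes beside the condition, so the conditions stand on the sheet that the coordinator uses. The Randomization section gives the steps in some detail and mentions no masking of later rows. That later rows can be read is an inference from this description; the article neither states nor excludes it.

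**2. Is there anything left to influence?** The order rule ties each row to completion of the baseline appointment, which limits reshuffling afterwards. Three openings remain beforehand.
- Encouragement: the coordinator is the contact for enquiries.
- Eligibility: many criteria are objective (HbA1c, measured BMI), but some need judgement, such as inability to do regular moderate activity or plans for bariatric surgery (Participants). The medical exam and stress test fall at the assignment appointment, so a decision on eligibility can still be open when the next row is known.
- Timing: the time of the appointment decides who takes the next row. The article does not say who books appointments.

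**3. What does the code contain?** The sentence on the code follows the one that lists date, initials and condition. The natural reading is that all three form the code; date and initials alone is also possible. On either reading the code is partly identifying. On the first it also reveals the arm.

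**4. Do assessors see it?** The article says that they are blind. It does not say that the code is on outcome forms, that assessors see the sheet, or that the coordinator measures outcomes.

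**5. Size.** The plan gives no figure on this point. The Sample size section supplies only a yardstick: SD 4.3 and a 95% CI half-width of 1.5 points. This reproduces: n = 2 × (1.96 × 4.3 / 1.5)² = 63.1, rounded up to 64 per group.

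For illustration only, suppose a fraction f of places in each arm goes to people whose expected loss is d points above average in one arm and d points below in the other. Then bias = f·d + f·d = 2fd. Both inputs are assumptions.

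| f | d = 1 | d = 2 | d = 3 |
|---|---|---|---|
| 0 | 0 | 0 | 0 |
| 0.05 | 0.1 | 0.2 | 0.3 |
| 0.10 | 0.2 | 0.4 | 0.6 |
| 0.20 | 0.4 | 0.8 | 1.2 |

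The range runs from nothing to 1.2 points, against an expected difference of 3 points. It shows why concealment is worth having and is no estimate for this trial.

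**The case against.** The strongest reply is that much here is inference. The article does not say that later rows are exposed, and the full protocol, which is not shown, may describe masking. The coordinator writes on the sheet only after a condition is assigned. Assignment already follows baseline, behind an online screen, a laboratory test, a measured BMI and a medical exam. Nothing says that the coordinator books appointments. The primary outcome is read from a digital scale to 0.1 kg, which leaves an assessor little room.

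Much of this stands, and it rules out three stronger readings that a reader might infer.
- *The next allocation is known with certainty.* The text supports only that it can be known, since masking is neither stated nor excluded.
- *Assessor blinding is broken.* No passage puts the code or the sheet in front of assessors, so this is a conditional risk.
- *The bias has a particular size.* The illustration needs steering in opposite directions in the two arms by someone able to judge prognosis. The documents support neither the fraction nor the gap.

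What the reply does not remove is the core. A condensed article may leave detail to a fuller document, but this one sets out the mechanism, and the mechanism set out has the recruiting contact working from a sheet that carries the conditions. The order rule and the objective criteria narrow the opening without closing it.

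**Conclusion.** The procedure as described lacks allocation concealment. Followed exactly, it lets the next arm be known before enrolment and so permits selection bias in the primary comparison. The size of any such bias is unknown, and the article gives no evidence that steering took place. The conclusion rests on one inference, that later rows of the sheet are readable by the coordinator. If they are masked, the point reduces to saying so.

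The code is a secondary matter: it appears to include the condition, and it would matter for blinding only if it is used on outcome records. Overall this is a cheap improvement, worth making while recruitment is open.

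**What to change.** For all remaining participants:

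1. Have the list held by someone not involved in recruiting or screening, or place it in a locked web module or in sequentially numbered opaque sealed envelopes.
2. Release each allocation only after that person's eligibility and baseline data are recorded. The article already ties assignment to completion of baseline; what is new is that the next allocation cannot be seen before then.
3. Put an arbitrary study ID with no condition, date or initials on every outcome form, and keep the link file from assessors.

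If masking is already in place, or assessors never see the code, a sentence in the Randomization section saying so would settle that part.

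The cost is a short amendment, minor administration and care in linking old and new IDs. The article does not show whether a team member outside recruitment is available; envelopes or a web module are alternatives if not. Sample size, visits and intervention do not change. Participants already allocated are not protected, and the article does not say how many they are.

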## Trial status

The RCT began participant recruitment in April 2013 and the first groups started in November 2013. Recruitment is currently (May 2014) ongoing until the required sample size is reached.

## Discussion

In order to meet the large needs for weight loss programs, effective group-delivered, shortened versions are required. The described intervention protocol provides a detailed description of the content and delivery of an RCT aimed to test the effectiveness of an enriched GLB program. Incorporating habit formation techniques could ultimately allow reducing the contact frequency and length of lifestyle modification programs, which would reduce their costs and enable wider dissemination. The habit formation tools integrated into the standard GLB are implementation intentions and mental practice, techniques proven effective for changing and sustaining new health behaviors.
